#### Muscle strength

Maximal isometric knee extension and flexion strength will be measured using dynamometry (Biodex system V.4X, Biodex Medical Systems, New York). The measurements will be expressed as the maximal voluntary contraction (MVC) in Newton meters (Nm). Prior to the measurement, participants will engage in a 5-minute warm-up on a stationary bicycle. Participants will be seated with their knees flexed at a 60-degree angle and their hips at a 90-degree angle, ensuring stability by securing straps to prevent undesired movements. To familiarize participants with the technique, one submaximal contraction will be performed prior to the measurement. Subsequently, three 5-second MVCs will be executed, with a 30-second rest interval between each contraction. The assessment of knee extension and flexion strength will start with the left leg, followed by measurements of the right leg. There will be a minimum of 2 min rest between the knee extension and flexion measurement. The measurement will be followed by a 5-minute cool down on a stationary bicycle. The highest torques of each leg will be used for analysis.

#### Mixed muscle fractional synthesis rates

Muscle biopsies will be obtained on day 0 and day 10 utilizing the percutaneous needle biopsy technique, as previously described by Bergström et al. [37], with a modified needle (Maastricht Instruments). The biopsies will be obtained from the middle region of the vastus lateralis muscle, 15 cm above the patella and approximately 2 cm below the fascia entry point. In short, the skin and muscle fascia will be locally anesthetized using Lidocaine (20 mg/ml) with Adrenaline (0.01 mg/ml). After approximately 10 min, a small incision of ca. 0.5 cm will be made in both the skin and fascia. Subsequently, the needle will be carefully inserted into the muscle. Using a syringe, a vacuum will be applied to the needle to collect small muscle samples of approximately 50–100 mg. Following the biopsy procedure, the incision will be closed using adhesive strips and covered with a plaster. Furthermore, a pressure bandage will be applied with multiple layers of gauze placed between the incision and the bandage. Subsequently, the muscle biopsies will be dissected carefully and any visible non-muscle material will be removed. The muscle samples will immediately be frozen in liquid nitrogen and stored at −80˚C until further analysis. For the assessment of plasma free ^2^H-alanine enrichments, blood samples will be collected on day − 1, 0 and 10 in EDTA-containing tubes and centrifuged at 1000 g for 10 min at 4 ˚C to obtain the plasma aliquots. Additionally, saliva samples will be collected to assess body water deuterium enrichment. A background saliva sample will be collected before the first D_2_O dose on day − 1. Subsequently, saliva will be collected daily during the subsequent 10 days, in the morning before breakfast. Participants will be instructed to place a cotton swab in their mouth for approximately 1 min to saturate the cotton swab with saliva and to store the saliva samples in their freezer at home until their next visit. After the samples are collected by the research team, a syringe will be used to depress the swab to extract the saliva into a sample tube. All samples will be frozen in liquid nitrogen and stored at −80˚C until further analysis.

In the obtained muscle tissue, mixed muscle protein bound ^2^H-alanine enrichment (expressed as MPE) will be assessed using a gas chromatography-isotope ratio mass spectrometer (MAT 253; Thermo Fisher Scientific, Bremen, Germany) equipped with a pyrolysis oven using a 60-m DB-17MS column and 5-m precolumn (No. 122–4762; Agilent) and GC-Isolink. Gas-chromatography-mass spectrometry (Agilent 5975 C MSD & 7809 A GC, Wilmington DE) will be used to measure plasma free ^2^H-alanine enrichment. Body water deuterium enrichments will be assessed using gas chromatograph-combustion-isotope ratio mass spectrometry (Micromass Optima IRMS fitted with a Multiprep and Gilson auto-injector; Micromass, Manchester, UK). The analyses will be performed at the Stable Isotope Research Centre (SIRC, Maastricht University Medical Centre+ (MUMC+), Maastricht, The Netherlands) and have been described in detail previously [38].

Mixed muscle FSR will subsequently be determined using the standard precursor-product calculation [38]:$$\mathrm{FSR}\left(\%\mathrm{day}\right)=\left(\frac{{\mathrm E}_{\mathrm m2}-{\mathrm E}_{\mathrm m1}}{{\mathrm E}_{\mathrm{precursor}}\mathrm{xt}}\right)\times100\%$$

Where *E*_m2_-*E*_m1_ represents the change in mixed muscle protein-bound ^2^H-alanine enrichments between the muscle biopsy samples taken on day 0 and day 10; *E*_precursor_ represents the plasma free ^2^H-alanine enrichment; and *t* represents the time between the biopsies taken before and at the end of the ten day measurement period.

#### Bone mineral density and bone turnover markers

Bone mineral density (BMD; g/cm^2^) will be measured at baseline and after 12 weeks using Dual X-Ray Absorptiometry (DEXA; GE Healthcare Prodigy Pro). Participants will be instructed to lie down on a table and to remain motionless during the scan. First, a total body scan will be performed to assess total body and spine BMD. Subsequently, a separate scan of each hip will be made. Additionally, blood samples will be collected at baseline, after 6 and after 12 weeks in EDTA containing tubes to assess the levels of insulin-like growth factor 1 (IGF-1), parathyroid hormone (PTH), bone resorption marker cross-linked C-telopeptide of type I collagen (CTX) and bone formation marker procollagen type I N-propeptide (PINP). Since CTX levels are highly affected by circadian rhythm, time of blood sampling will be the same for each subject and each measurement, and before 10 am [39]. The EDTA containing tube will be centrifuged for 15 min at 1000 g and 4 ˚C to obtain plasma aliquots. Plasma CTX, PINP, IGF-1 and PTH levels will be assessed using a chemiluminescent immunoassay. Plasma PTH levels will be analyzed on the same day as blood collection.

#### Metabolic profile and hs-CRP

Blood will be collected in Li-heparin and EDTA containing tubes at baseline, after 6 weeks and after 12 weeks to assess insulin levels and metabolic profile, respectively. After centrifugation at 3000 g and 22 ˚C for 8 min, plasma aliquots will be collected from the Li-Heparin tube for the assessment of insulin. The EDTA containing tube will be centrifuged for 15 min at 1000 g and 4 ˚C. Subsequently, aliquots of EDTA plasma will be collected for the determination of hs-CRP and metabolic profile. All plasma aliquots will be immediately frozen in liquid nitrogen and stored at −80˚C until further analysis. Metabolic profile will be analyzed via the commercially available high-throughput proton Hydrogen-1 Nuclear Magnetic Resonance (^1^H-NMR) metabolomics platform of Nightingale Health ltd. (Helsinki, Finland), as described elsewhere [40]. Insulin levels will be assessed using a solid-phase enzyme-labeled chemiluminescent immunometric assay.

#### Micronutrient status

Blood samples will be collected in serum, Li-Heparin, and EDTA containing tubes at baseline and after 12 weeks. The EDTA containing tube will be transported to the hospital Gelderse Vallei in Ede on the day of blood sampling for immediate analysis of hemoglobin levels using the cyanmethemoglobin method. The serum tube will be centrifuged one hour after sampling for 8 min at 3000 g and 22 ˚C. Serum aliquots will be collected for the analysis of vitamin D. The Li-Heparin tube will be centrifuged immediately after sampling for 8 min at 3000 g and 22 ˚C. Plasma aliquots will be collected for the analysis of ferritin and methylmalonic acid. All samples will be immediately frozen in liquid nitrogen and subsequently stored at −80˚C until further analysis. Vitamin D will be assessed using liquid chromatography tandem mass spectrometry. Ferritin and methylmalonic acid will be assessed using a chemiluminescent immunoassay and chromatography-tandem mass spectrometry, respectively.

#### Gastrointestinal health

Faecal samples and two aliquots of blood plasma will be collected at baseline and after 12 weeks from participants assigned to the VEG and OMNI groups. Faecal samples will be collected by the participants at home using a sterilized paper faecal bag. Subsequently, the samples are placed in sealed insulated containers by the participants, sealed in biohazard bags and stored in the freezer of the participants until their subsequent visit. Participants will be instructed to collect the faecal samples within 24 h prior to their subsequent visit to the research unit. The microbial DNA will be isolated from the faeces samples using Qiagen AllPrep DNA/RNA Mini kit (Qiagen) in combination with mechanical lysis. Metagenomic sequencing reads mapped to the human genome or aligned to Illumina adapters will be identified and removed using KneadData. The metagenomics data will reveal the taxonomy and the function of specific genes. Furthermore, blood samples will be collected in EDTA containing tubes and centrifuged at 1000 g and 4 ˚C for 15 min to obtain two aliquots of plasma. Untargeted and targeted metabolomics will be performed using LC/GC-MS on both the plasma and faecal samples. Targeted metabolomics will monitor tryptophan, tyrosine and branched-chain amino acid pathways, and oxidized amino acids. By contrast, untargeted metabolomics will explore unknown metabolic pathways and gut microbial metabolites to correlate gut microbiota functionality and circulating metabolites. By combining metagenomics with metabolomics data, and bioBakery workflow (KneadData, HUManN, MetaPhlAn, StrainPhlAN), we will investigate microbial communities using standardized and validated tools. The fusion of metagenomics and metabolomics data using Mmvec, MIMOSA2, and lineal models will link metabolites with microorganisms at strain/species level and functions.

The gastro-intestinal symptom rating scale (GSRS) questionnaire will be filled out by all participants at baseline and at the end of the intervention to assess the effect of the intervention on gastro-intestinal symptoms [41, 42]. The questionnaire includes 15 questions covering 5 common symptom clusters on a 7-point likert scale and takes approximately 3 to 5 min to fill out. These clusters are abdominal pain, reflux, indigestion, constipation and diarrhoea. Using this questionnaire, the participants will rate their symptoms over the past week.

#### Blood pressure

Systolic and diastolic blood pressure (mmHg) will be assessed at baseline, after 6 and 12 weeks. The measurement will be performed after an overnight fast using an ambulatory blood pressure monitor (Omron Healthcare Europe B.V.; OMRON automatic digital blood pressure monitor HEM-907; CE-certified). Participants will be instructed not to drink coffee, smoke or perform vigorous exercise in the 60 min before the measurement and will not be allowed to speak during the measurement. Blood pressure will be measured three consecutive times with 1 min rest intervals, after resting on a chair for 5 min. The mean of the second and third measurement will be used for analysis. A fourth measurement will be performed if the participant speaks or moves during a measurement or when a difference of 10 mmHg is observed between the second and third measurement. In those cases, the mean of the third and fourth measurement will be used for analysis.

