### Study outcomes

#### Thigh muscle volume and fat distribution

An overview of all study outcomes is presented in (Table 2). The primary outcome thigh muscle volume (L), and secondary outcomes thigh muscle fat infiltration (MFI; %), liver fat fraction (LFF; %), visceral adipose tissue (VAT; L) and abdominal subcutaneous adipose tissue (ASAT; L), will be assessed using a neck to knee MRI scan (Philips Ingenia Elition 3 T X, Philips Healthcare, Best, the Netherlands) at baseline and after 12 weeks. T1-weighted transverse images will be obtained using a dual-echo FFE scan sequence for the quantification of thigh muscle volume, MFI, VAT, ASAT, and LFF. Participants will enter the scanner head-first. Parameters for the thighs will be: Repetition time (TR), shortest; echo times (TE), shortest; flip angle, 10⁰. Parameters for the abdomen will be: TR, shortest; TE, shortest, 1 ms; flip angle, 10⁰. Image resolution for the scans covering the thighs is 1.84 × 1.84 × 4 mm, and for the scans covering the abdomen is 3 × 3 × 6 mm.

**Table 2 Tab2:** Overview of the outcome measures

Outcome	Method			Time			
		Screening	Baseline	Day 10		Week 6	Week 12
Primary							
Thigh muscle volume	MRI-scan		X				X
Secondary							
Thigh muscle fat infiltration	MRI-scan		X				X
Fat distribution	MRI-scan; DEXA-scan		X				X
Muscle strength	Biodex		X				X
Mixed muscle FSR	Muscle biopsy		X	X			
	Blood sample		X	X			
	Saliva sample		Daily for 11 days				
Bone mineral density; lean mass	DEXA-scan		X				X
Bone turnover markers	Blood sample		X			X	X
Metabolic profile	Blood sample		X			X	X
Blood pressure	Blood pressure monitor		X			X	X
Micronutrient status	Blood sample		X				X
hs-CRP	Blood sample		X				X
GI health	Stool sample*		X				X
	Blood sample*		X				X
	GSRS		X			X	X
Body mass	Scale	X	X	X		X	X
Dietary intake	Food diary		X	X		X	X
Other							
Participant characteristics	Questionnaire	X					
Height	Stadiometer	X					
WOMAC-index**	Questionnaire		X				X
DNA methylation	Blood sample		X				X
Handgrip strength	Hand dynamometer		X				
Physical activity levels	Accelerometery		Daily for 17 days				Daily for 7 days***
	Activity diary		Daily for 17 days				Daily for 7 days ***
Compliance	Attendance nutrition information meetings	Monthly at each information meeting					
	Attendance RE	Twice a week at each RE session					
	Food diary		X		X	X	X
	Accelerometry		Daily for 17 days				Daily for 7 days***

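### A third blood pressure reading disturbed by speech or movement stays in the analysed mean, because the fourth-reading rule always averages readings 3 and 4

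*Protocol article*

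**What the plan says.** The Blood pressure section of the protocol article sets out the whole procedure.

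- Visits: "Systolic and diastolic blood pressure (mmHg) will be assessed at baseline, after 6 and 12 weeks".
- Routine readings: "Blood pressure will be measured three consecutive times with 1 min rest intervals, after resting on a chair for 5 min".
- Default value: "The mean of the second and third measurement will be used for analysis".
- Measurement condition: the participant "will not be allowed to speak during the measurement".
- First trigger for an extra reading: "A fourth measurement will be performed if the participant speaks or moves during a measurement". The text does not limit this to a particular reading.
- Second trigger: "when a difference of 10 mmHg is observed between the second and third measurement".
- Value analysed after either trigger: "In those cases, the mean of the third and fourth measurement will be used for analysis".

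No sentence says that the disturbed reading itself is set aside. Table 2 places blood pressure (method entry "Blood pressure monitor") in its block of secondary outcomes, at baseline, week 6 and week 12.

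**The concern.** An extra reading after speech or movement only makes sense as a substitute for the reading that was spoiled. The article forbids speech during the measurement and orders another reading when it happens, so it treats such a reading as compromised. Yet the pair that is then analysed is fixed by position, not by which reading was compromised. When the disturbance falls on reading 3, the plan pays for a replacement, keeps the reading that needed replacing, and discards a sound one. At stake is avoidable measurement error in a secondary outcome at any of three visits.

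**Working it through.** The plan gives no figure to reproduce here, so the check consists of following the written rule through each case.

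**Inputs.** All come from the Blood pressure section: three routine readings, default pair 2 and 3, a fourth reading after disturbance of any reading or after a 10 mmHg gap between readings 2 and 3, and then always the pair 3 and 4.

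**Cases, assuming one disturbed reading per visit**

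| Event | Pair analysed | Is a disturbed reading in the pair? |
|---|---|---|
| Reading 1 disturbed | 3 and 4 | No |
| Reading 2 disturbed | 3 and 4 | No; the rule does what it should |
| Reading 3 disturbed | 3 and 4 | Yes, at weight 1/2; undisturbed reading 2 is dropped |
| 10 mmHg gap between 2 and 3, none disturbed | 3 and 4 | No; the latest pair is used |

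Only the third row fails.

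**Size in one visit.** Let x3 and x4 be the values that undisturbed readings would have given, and b the error that the disturbance adds to reading 3. The analysed value is

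((x3 + b) + x4)/2 = (x3 + x4)/2 + b/2.

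The visit value therefore carries b/2. The documents do not give b. Over an assumed range:

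- b = 5 mmHg: 5/2 = 2.5 mmHg
- b = 10 mmHg: 10/2 = 5 mmHg
- b = 15 mmHg: 15/2 = 7.5 mmHg

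Using readings 2 and 4 instead, the disturbance error is 0.

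**Illustration with assumed readings.** Take readings 2, 3 and 4 as 130, 142 (disturbed) and 130 mmHg, so b = 12. The written rule gives (142 + 130)/2 = 136 mmHg. The undisturbed pair gives (130 + 130)/2 = 130 mmHg. The difference is 6 mmHg, which is 12/2.

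**Size in an arm mean.** The Sample size calculation section has 24 recruited and 20 needed per group. One affected participant at one visit moves the arm mean by between 2.5/24 = 0.10 mmHg (b = 5, 24 per arm) and 7.5/20 = 0.38 mmHg (b = 15, 20 per arm). With b = 10 the shift is 5/24 = 0.21 or 5/20 = 0.25 mmHg. How many participants would be affected cannot be derived from the documents.

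**The case against.** The best counter-argument is that the Study overview section says measurements follow standard operating procedures, which are not shown and which a journal article condenses. Staff may be told there to repeat a disturbed reading on the spot. That is possible, and it lowers the likelihood of harm. It does not remove the point: the article states trigger, action and analysed value in full, and a procedure that set a disturbed third reading aside would contradict the published rule.

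It is also fair to say that the effect is small, that the article never calls a disturbed reading invalid, and that the secondary label rests on Table 2 alone: blood pressure appears neither among the secondary objectives in Table 1 nor in the abstract's list of secondary outcomes. All of that stands, and it limits how much weight the point deserves.

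A reader might infer more than the text supports, in four ways.

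- *That a disturbed first reading is also mishandled.* Readings 3 and 4 are then both undisturbed. Dropping reading 2 is inefficient at worst and puts no disturbed value into the outcome.
- *That the gap trigger applies only at exactly 10 mmHg.* The ordinary meaning is a threshold, and no operator would take a fourth reading at 10 mmHg but skip it at 15.
- *That readings 3 and 4 are the wrong choice after a large gap.* Using the latest pair is a coherent rule; averaging readings 2 to 4 instead would be a matter of preference.
- *That open allocation turns this into bias between arms.* The Randomization section does say that staff know the allocation, but the monitor is automatic, the rule is the same in every arm, and nothing suggests that disturbance of reading 3 differs by arm.

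**Conclusion.** The point holds for one case. When speech or movement disturbs reading 3, the written rule keeps that reading at weight 1/2 and discards an undisturbed reading 2. The visit value then carries b/2, or 2.5 to 7.5 mmHg if b is assumed to lie between 5 and 15 mmHg. This rests on the literal text of the article, on a single disturbed reading per visit, and on an assumed error size; its frequency is unknown. The likely consequence is minor extra noise in blood pressure. The primary outcome, the sample size and both primary contrasts are unaffected. It is a small correction worth making because it is nearly free.

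**What to change.** Amend the averaging rule in the Blood pressure section, and in the measurement procedure if it reads the same way, to say:

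1. A reading during which the participant spoke or moved is not used. The mean of the last two undisturbed readings after the first is analysed: readings 2 and 4 if reading 3 was disturbed, readings 3 and 4 if reading 1 or 2 was.
2. If readings 2 and 3 are both undisturbed but the 10 mmHg trigger is met, readings 3 and 4 are analysed, as now.

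The disturbance rule should take precedence where both triggers apply, because a disturbed third reading can itself create the gap (as in the illustration, where readings 2 and 3 differ by 12 mmHg). The wording should also cover a visit with fewer than two undisturbed readings after the first.

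The cost is a sentence or two. If individual readings and notes of disturbance are stored, the rule can be applied to visits already completed, before the analysis. If only the averages were kept, the affected visits cannot be corrected, and the rule can only be applied to later ones.

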#### Dietary assessment

Dietary intake will be assessed before the start of the intervention, at the beginning of the intervention, approximately halfway, and at the end of the intervention via three-day food records. The food records will be administered via a dietary assessment smartphone application (Traqq) [43]. The food records will cover two weekdays and one weekend day for each assessment period, which will be randomly assigned to each participant at each assessment period to allow for an even spread of dietary assessment throughout the week. Participants will receive a notification once in the morning on the day that they are assigned to report their dietary intake. After reporting of the food products, participants will be requested to enter the consumed amount and the eating occasion. The computation module of Compl-eat [44] will subsequently be used to calculate intake of food groups, energy, macro- and micronutrients by multiplying consumed amounts by energy or nutrient content using the Dutch Food Composition Database 2021, extended with the products that will be provided to the participants in this study. In case a participant has no (compatible) smartphone, the participant will list his or her dietary intake on a paper food diary, which will subsequently be transferred to Compl-eat by a member of the research team. Participants will be contacted for clarifications in case of obscurities in the dietary data. All records will be checked by a member of the research team for completeness, unusual consumed amounts, and notes.

#### Assessment of physical activity

Participants will wear an accelerometer (ActiGraph, Pensacola, Florida; CE: EN60601-1) on their hip during seven consecutive days before the start of the intervention, during the first 10 days of the intervention and during seven consecutive days in the last month of the intervention to assess physical activity levels. Additionally, participants will be instructed to record their activity in a diary during the days that the accelerometer is worn.

#### Other study outcomes

Baseline participant characteristics will be collected during screening and at baseline using questionnaires. Baseline characteristics include demographics (gender, age, ethnicity, living situation, education, smoking habits, alcohol use), medical history, lifestyle habits, body mass (kg), height (m), and medication and supplement use. Body mass will be measured to the nearest 0.1 kg during screening, at baseline, after 6 weeks and after 12 weeks using a calibrated digital scale. Height will be measured to the nearest 0.01 m during screening using a wall mounted stadiometer. Handgrip strength (kg) will be measured at baseline with the use of a hand dynamometer (Jamar, Jackson, Michigan). Both hands will be measured three consecutive times to the nearest 0.5 kg. During the measurement, participants will be seated in an upright position with the arm in a 90-degree angle. Furthermore, whole blood samples will be collected in Li-Heparin tubes at baseline and week 12 to assess DNA methylation. DNA methylation will be assessed using standard bisulfite methods and assays like Illumina 450 K, EPIC 850 K, or largely similar methods. In support of the DNA methylation assessment, whole blood samples will be collected in EDTA containing tubes and analyzed to assess the differentiation of leukocytes (basophils, eosinophils, segmented leukocytes, lymphocytes, and monocytes) on the same day of blood collection using hemocytometry. Additionally, participants that report to have (osteo)arthritis at the moment of screening, will be asked to fill out the Western Ontario and McMaster Universities Arthritis Index (WOMAC) at baseline and after 12 weeks [45, 46].

